### Rescue therapy

For participants with poor bowel preparation, the endoscopist will determine whether to continue colonoscopy. If colonoscopy cannot be performed because of insufficient bowel preparation, bowel preparation can be performed again free of charge. Moreover, in case of serious adverse reactions, the investigator will provide prompt and appropriate treatment based on the diagnosis and documents related to all treatment options.

### Safety assessments

Responses of all events related to adverse reactions must be recorded, including the duration of symptoms or signs and outcomes. All adverse events related to bowel preparation and colonoscopy in a case report form (CRF), including nausea, vomiting, bloating, abdominal pain, dizziness, vertigo, sweating, dry mouth, and electrolyte imbalance, must be recorded.

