**Methods:**

This is a randomized, double-blind, single-center clinical study. We randomly assigned 690 participants to groups each administered 3 L of polyethylene glycol (PEG), 30 mL of hemp seed oil and 2 L of PEG, or 30 mL of hempseed oil, 2 L of PEG, and 1000 mL of 5% sugar brine. The Boston Bowel Preparation Scale was considered the primary outcome measure. We evaluated the interval between consumption of bowel preparation and first bowel movement. Secondary indicators included the time of cecal intubation, detection rate of polyps and adenomas, willingness to repeat the same bowel preparation, whether the protocol was tolerated, and whether there were adverse reactions during bowel preparation and were evaluated after counting the total number of bowel movements.

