### Objectives

This study aimed to investigate the potential of 30 mL of hemp seed oil in enhancing bowel cleansing. The study also evaluated the effect of reducing PEG by half by adding hemp seed oil and 5% sugar brine on reducing the adverse effects of bowel preparation and increasing the patients’ tolerance of PEG.

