### Recruitment, randomization, and blinding

Investigators trained for the study and authorized by the principal investigator will assess the candidates according to the inclusion and exclusion criteria on the day before the colonoscopy. After eligible participants are identified, written informed consent will be obtained from each eligible patient, next of kin, or legal representative. On the consent form, participants will be asked whether they agree to the use of their data and biological specimens. Participants will be asked to agree to the research team sharing relevant data with regulatory authorities as appropriate. Researchers should collect clinical data, including gender, age, weight, BMI, history of the previous colonoscopy, history of abdominal surgery, cardiovascular and neurological diseases, and long-term use of certain drugs.

Initially, the SPSS version 22.0 software will be used to generate random sequences, and these will be subsequently put in an opaque envelope. The independent statistical expert used a computer to generate random numbers, and the participants were assigned to the following 3 groups in a 1:1:1 ratio, numbered sequentially after random assignment: A, 3L PEG; B, 30 mL of hempseed oil and 2 L of PEG; and C, 30 mL of hemp seed oil, 2 L of PEG, and 5% sugar brine. Moreover, researchers, endoscopic physicians, and participants will all be blinded during the examination to eliminate bias as much as possible.

At the end of the study, unblinding will be carried out by the principal investigator. The first unblinding will be conducted to uncover the groups of participants, followed by statistical analysis to clarify the differences between the groups, and a second unblinding will be conducted to further clarify the specific groups. When an emergency, such as a serious adverse event, threatens the safety of a subject and the subject’s grouping must be known, an emergency unblinding would be conducted. The unblinding of the specific time, reason, and name of the executive of the emergency will be timely recorded.

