### Study protocol

All subjects undergoing colonoscopy should start a no-pigment, low-residue, low-fiber diet 3 days before examination and fast at 18:00 the night before the examination. If hypoglycemia or other discomforts occur due to hunger on the same day, oral colorless vitamin drinks or candy bars can be taken to enhance tolerance. Moreover, to allay the participants’ fear of intestinal preparation, researchers should explain the purpose of colonoscopy, importance of adequate intestinal preparation, and potential adverse events that may occur during intestinal preparation.

Figure 2 depicts the drug use schemes of the 3 groups. The oral intestinal preparation process under the guidance of researchers in the 3 L of PEG group was as follows: one bag of PEG and 1 L of clear fluids was taken orally at 22:00 the day before the examination, the second bag was taken 4–6 h before the examination, and the third bag of PEG was taken half an hour later (Fig. 2A). As for the 30 mL of hemp seed oil and 2 L of the PEG group, patients orally took 15 mL of hemp seed oil in divided doses at 20:00 and 22:00 1 day before the examination, the first bag of PEG and 1 L of clear fluids 4–6 h before the examination, and the second bag of PEG half an hour later (Fig. 2B). Regarding the 30 mL of hemp seed oil, 2 L of PEG, and 5% sugar brine group, patients orally took 15 mL of hemp seed oil in divided doses at 20:00 and 22:00 1 day before the examination, the first bag of PEG and 1000 mL of 5% sugar brine 4–6 h before the examination, and another bag of PEG half an hour later (Fig. 2C). In the study, participants were free to drink clear fluids after the commencement of bowel preparation. The study schedule is shown in Fig. 3.

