#### Secondary outcomes

Adverse reactions that occur during bowel preparation are the secondary outcome indicators of the study. We evaluated the interval between taking bowel preparation and the first bowel movement, the total number of bowel movements completed, time of cecal intubation, detection rate of polyps and adenomas, willingness to repeat the same bowel preparation, whether the protocol is tolerated (0 points for no discomfort; 1 point for mild discomfort; 2 points for ability to tolerate; 3 points for not being able to tolerate), and adverse events.

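### The safety outcome is given three different scopes, and case report form entry depends on relatedness with no stated phase of onset, which leaves an avoidable route to bias or dilution

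*Protocol article*

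**What the plan says.** The protocol article describes the safety outcome in three ways.

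- **Preparation period only.** Secondary outcomes opens with "Adverse reactions that occur during bowel preparation are the secondary outcome indicators of the study". The Methods part of the abstract agrees: "whether there were adverse reactions during bowel preparation".
- **No limit.** The list in Secondary outcomes ends with the tolerance score and a further item: "3 points for not being able to tolerate), and adverse events". No period or cause is attached to it.
- **Recording rule.** Safety assessments requires "All adverse events related to bowel preparation and colonoscopy in a case report form (CRF), including nausea, vomiting, bloating, abdominal pain" and further named symptoms. On detail it says: "Responses of all events related to adverse reactions must be recorded, including the duration of symptoms or signs and outcomes". Time or phase of onset is not among the details named, and neither an assessor nor a criterion for relatedness is given.

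Safety is part of the stated aim. Objectives refers to the effect of the modified regimen "on reducing the adverse effects of bowel preparation and increasing the patients’ tolerance of PEG".

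**The concern.** The recording rule fits neither version of the outcome. It is wider than the preparation-period outcome, because it takes in events from the colonoscopy. It is narrower than the unrestricted adverse-event item, because it asks only for related events.

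Two consequences are possible.

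1. **Attribution.** To record related events, someone must decide what is related. Under Study protocol the intakes differ visibly. Groups B and C take oil the evening before ("patients orally took 15 mL of hemp seed oil in divided doses at 20:00 and 22:00 1 day before the examination"), and no matching oil is described for group A. Group A takes three bags of PEG and the others two, and only group C takes sugar brine. Anyone who knows the intake may attribute a symptom differently by group. An event left out at entry is lost to any later analysis.
2. **Phase.** Bloating, abdominal pain, dizziness and sweating are on the list and can also follow the colonoscopy, which all groups undergo. Data management adds telephone and questionnaire follow-up after colonoscopy, so some symptoms may be collected after both exposures. Without an onset mark, the preparation-period outcome cannot be reliably separated out.

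**Working it through.** **Comparison of scopes**

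| Source | Period | Cause |
|---|---|---|
| Secondary outcomes, opening; abstract | preparation | reaction (implies relatedness) |
| Secondary outcomes, end of list | none stated | none stated |
| Safety assessments | preparation and colonoscopy | related |

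The period differs between the first and third rows, and the cause differs between the second and third. Recording related events does not in itself conflict with an outcome called adverse reactions. The conflict over cause is with the unrestricted item.

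**Inputs for an illustration**

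- From the article: 690 participants (Sample size) allocated 1:1:1 (Recruitment, randomization, and blinding), so 690 / 3 = 230 per group; two-sided 0.05 and a chi-square test for categorical secondary outcomes (Statistical analysis).
- Not in the article, so assumed: every adverse-event rate and every attribution share below. The article gives no safety power or event rate, so there is no figure of its own to reproduce.

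Power for rates p1 and p2, with mean p̄ and n = 230:

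Φ{ [ |p1 − p2|·√n − 1.96·√(2p̄(1 − p̄)) ] / √( p1(1 − p1) + p2(1 − p2) ) }

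For 30% and 20%: (0.10 × 15.166 − 1.96 × 0.6124) / 0.6083 = 0.52, and Φ(0.52) = 69.8%.

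**Dilution, if the phases were counted together.** Let c be a colonoscopy event rate, the same in each group and independent of preparation events. Then p′ = 1 − (1 − p)(1 − c), and the difference shrinks by the factor (1 − c).

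| c | 30% vs 20% becomes | Power | 40% vs 28% becomes | Power |
|---|---|---|---|---|
| 0 | 30.0 vs 20.0 | 69.8% | 40.0 vs 28.0 | 77.7% |
| 5% | 33.5 vs 24.0 | 61.5% | 43.0 vs 31.6 | 71.6% |
| 10% | 37.0 vs 28.0 | 54.0% | 46.0 vs 35.2 | 65.6% |
| 20% | 44.0 vs 36.0 | 41.7% | 52.0 vs 42.4 | 54.1% |
| 30% | 51.0 vs 44.0 | 32.4% | 58.0 vs 49.6 | 43.9% |

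**Attribution, if it differed by group.** Recorded rate = true rate × share judged related. Take a true rate of 30% in both groups.

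- 90% judged related in both: 27% vs 27%, no false difference.
- 95% vs 85%: 28.5% vs 25.5%, a false difference of 3.0 points, significant in about 11% of trials.
- 90% vs 70%: 27% vs 21%, a false difference of 6.0 points, significant in about 33% of trials.

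**The case against.** The strongest reply is that the article states neither pooling nor a biased filter.

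- **Pooling.** A reader might infer that preparation and colonoscopy events are analysed as one count. The text does not support this. Safety assessments says what to record, and the abstract and the opening of Secondary outcomes both keep the outcome to the preparation period. Collecting more widely than the outcome window is ordinary safety practice. This objection stands, so the dilution figures are conditional.
- **Onset.** Data management says the case report form held all data required, and the form is not shown. It may carry an onset field. This stands in part: the article names the details to capture and omits this one, but that does not show it is missing from the form.
- **Who judges.** A reader might infer that the staff who guided intake decide which symptoms are entered. Nothing says so, and no formal causality assessment is described. The article also states that "researchers, endoscopic physicians, and participants will all be blinded during the examination", and the named symptom list limits discretion. This stands as far as the identity of the assessor goes. The blinding statement refers to the examination, though, and the intakes as described are visibly different to those taking them.
- **Size.** Every rate is assumed. Patients with preparation symptoms may also be those with symptoms afterwards, and such overlap would reduce the dilution. An any-event composite is assumed too. This stands.
- **Importance.** The outcome is secondary. The abstract's Discussion, Objectives and the main Discussion tie the reduction in adverse effects mainly to the combination with sugar brine (group C). The Introduction's hypothesis is the absence of obvious adverse effects, not fewer of them. This stands and limits how much rests on the point.

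What the reply does not remove is that the scopes differ in the text and that relatedness is a written condition of the recording rule.

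**Conclusion.** The point holds as a conflict of definition and a weak recording rule. Secondary outcomes and Safety assessments describe different sets of events. The relatedness condition can let attribution differ by group where regimens are visibly different, and an omission at entry is permanent.

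It would go too far to say that the safety contrast is diluted or biased. Dilution requires the two phases to be counted together, which the article does not say. Bias requires attribution to differ by group, which it does not show. The size cannot be computed from the document. The figures above indicate only what could happen under assumed rates, independence of the two phases and an any-event outcome. The change is still worth making, because it closes an avoidable route to bias in a stated objective at little cost.

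**What to change.** Reconcile Secondary outcomes and Safety assessments under one rule:

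- record every adverse event from first study intake, whatever its presumed cause;
- mark onset as before or after the start of colonoscopy;
- count only events with onset before colonoscopy in the preparation-period outcome;
- report later events separately;
- keep relatedness as a descriptive item, not a condition of entry.

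If the case report form already holds time of onset, it is enough to say so and to state the counting rule. As described in Study protocol, first intake is at 20:00 in groups B and C and at 22:00 in group A. The window therefore opens two hours earlier in B and C; this is part of the regimens compared and should be stated.

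The cost is at most one onset field, a short outcome definition and slightly more events to record. Participants already enrolled can be covered only as far as their forms or source notes hold onset and unrelated events, and the report should say so.

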### Data management

To promote participant retention, we recruited participants through health promotion and followed up with them by telephone and questionnaires after colonoscopy. All data were recorded in CRF, which contained all data required for the study. Before formally using the data, relevant persons should be trained by experts. Only the researcher or relevant researchers are authorized to use EXCEL 2019 to collect, classify, and use the data. Data collection and analysis are supervised by the Ethics Committee of the First Hospital of Lanzhou University.

All researchers will follow professional confidentiality rules and must keep all personal and medical information of patients confidential. The paper clinical report form will be destroyed 3 years after the completion of the study. Personal patient information will be hidden, electronic data will be stored and encrypted, and access to databases will be restricted. All data management should be conducted by a designated data management team established by the principal investigator and an independent statistician.

### Protocol amendments

The study protocol has been approved by the Ethics Committee of the First Hospital of Lanzhou University. The protocol amendments will be submitted to the Ethics Committee for review, and the online clinical trial registry will be updated.

### Statistical analysis

In this study, we will adopt intent-to-treat and per-protocol methods to analyze all data. The basic information of patients is expressed by mean, median, and standard deviation. The chi-square test will be used to compare the categorical variables in the basic data of patients. In two independent samples, the Mann–Whitney *U*-test and Student’s test will be used for the comparison of continuous variables; the chi-square test will be used for the comparison of the main results; secondary outcomes will be compared using the chi-square test for categorical variables and Student’s *t*-test for continuous variables. All statistical analyses will be conducted with the 2-tailed test, and *P* < 0.05 will be considered statistically significant. We will make every attempt to collect complete information for all participants and avoid missing data. If necessary, missing data will be handled using multiple imputation. As no formal stopping rules have been specified for this study, no formal interim analyses are planned, and hence, no statistical testing will take place until the final analysis. All data were analyzed using SPSS 26 (SPSS Inc., an IBM Company, Chicago, IL).

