Therefore, we hypothesized that the oral administration of 30 mL hemp seed oil in stages could enhance the intestinal cleansing ability of PEG, decrease the dosage of PEG without any obvious adverse effects, and increase its acceptance. This trial aimed to determine the efficacy, safety, and tolerability of 2 L of PEG plus hemp seed oil in combination with 5% sugar brine for bowel preparation.

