### Trial design and setting

This is a double-blind, single-center, three-arm, non-inferiority study that will be conducted at the Surgical Endoscopy Center of the First Hospital of Lanzhou University from April 2022 to February 2023. Recruited participants will be randomly assigned to receive a combination of 3 L of PEG, 30 mL of hemp seed oil and 2 L of PEG, or 30 mL of hemp seed oil, 2 L of PEG, and 1000 mL of 5% sugar brine (Fig. 1).

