### Sample size

We calculated the expected sample size based on the preliminary extrapolation of the results of bowel preparation before the study began. According to the results of previous studies, when using 3 L PEG for bowel preparation, the qualified rate of bowel preparation was 80%. PEG was accepted as the standard preparation, and the aforementioned percentage was taken as a reference [18, 20, 37, 38]. Assuming the qualified rate of bowel preparation in this study is 85%, the alpha level was set to 0.05. When a sample size of 690 was calculated, a 5% difference between the three groups could be determined.

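### The design is declared non-inferiority, but the primary analysis is a two-tailed test of equality with no margin; unless a new regimen is significantly better, it gives no valid decision on non-inferiority

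*Protocol article*

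**What the plan says.** All references are to the protocol article.

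- **Trial design and setting:** "This is a double-blind, single-center, three-arm, non-inferiority study". The label appears only here; the Abstract and the Discussion describe the trial without it.
- **Statistical analysis:** "the chi-square test will be used for the comparison of the main results". The same section adds "All statistical analyses will be conducted with the 2-tailed test", with significance at P < 0.05, and names intent-to-treat (ITT) and per-protocol (PP) analyses.
- **Sample size:** for 3 L PEG, "the qualified rate of bowel preparation was 80" per cent; then "Assuming the qualified rate of bowel preparation in this study is 85" per cent. Also "the alpha level was set to 0.05", with no sidedness given. With 690 participants, "a 5% difference between the three groups could be determined". Power is not stated, and the 5 points are not called a margin.
- **Introduction:** the hypothesis is that the oil "could enhance the intestinal cleansing ability of PEG". The Abstract and the Objectives also word the aim as better cleansing, alongside using less PEG.

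No non-inferiority margin, confidence-interval criterion or non-inferiority decision rule appears in the article.

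**The concern.** A non-inferiority trial has to reject the hypothesis that the new regimen is worse than control by at least a stated margin. The planned chi-square test has equality as its null hypothesis. Failing to reject equality does not exclude an important deficit, and the article gives no margin to measure a deficit against. Applying the test in both the ITT and PP sets does not change what it tests.

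This is more than detail left to a fuller document. The article itself fixes the test, its sidedness and its threshold, and these do not match the design it declares.

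At stake is the trial's primary conclusion: whether a regimen with 2 L of PEG cleans acceptably compared with 3 L. Without a margin set in advance, the most probable outcome (P > 0.05) cannot be interpreted on that question, and a margin could be chosen after the data are seen.

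**Working it through.** **Inputs from the article.** Control rate 80%, assumed rate 85%, total 690 (Sample size); 1:1:1 allocation (Recruitment, randomization, and blinding), so 690/3 = 230 per arm; two-tailed P < 0.05 (Statistical analysis).

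**Assumptions.** Margins of 5 and 10 points; 80% power and one-sided 0.025 for non-inferiority; no dropout. The article gives none of these.

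**1. Which reading yields 690?**

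*Test of difference, 80% against 85%, two-sided 0.05, 80% power:*
n = [1.960·√(2·0.825·0.175) + 0.842·√(0.80·0.20 + 0.85·0.15)]² / 0.05² = (1.0532 + 0.4513)² / 0.0025 ≈ 906 per arm, or 2718 in total. This does not give 690.

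*Non-inferiority, control 80%, test 85%, assumed 5-point margin:*
n = (1.960 + 0.842)²·(0.16 + 0.1275) / (0.05 + 0.05)² = 7.849·0.2875 / 0.01 ≈ 226 per arm, or 678 in total. This is within 2% of 690.

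The second reading fits, but the fit does not identify the margin. For example, a 12-point margin with both rates at 80%, one-sided 0.025 and 90% power gives 234 per arm, or 702. So 690 cannot be confirmed from the stated inputs alone.

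**2. What the planned chi-square does at 230 per arm.** Power for 80% against 85%:
SE under the null = √(2·0.825·0.175/230) = 0.03543; SE under the alternative = √(0.2875/230) = 0.03536.
Power = Φ[(0.05 − 1.960·0.03543)/0.03536] = Φ(−0.55) = 0.29. A three-group chi-square with rates 80/85/85 has about 30%.

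Exact binomial enumeration of the pairwise two-sided test, control at 80%:

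| True rate, new regimen | P > 0.05 | Significant, new better | Significant, new worse |
|---|---|---|---|
| 85% | 71% | 29% | <0.1% |
| 80% | 95% | 2.5% | 2.5% |
| 75% | 75% | <0.1% | 25% |
| 70% | 30% | <0.1% | 70% |

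**3. What a non-significant result can hide.** Suppose 184/230 (80.0%) on control and 167/230 (72.6%) on a new regimen. Difference −7.4 points; pooled rate 351/460 = 0.763; z = −0.0739 / √(2·0.763·0.237/230) = −1.86, so P > 0.05. The 95% CI is −0.0739 ± 1.96·0.0395, about −15.1 to +0.4 points.

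**4. Power of a proper non-inferiority test at 230 per arm.** Power = Φ[(margin + true advantage)/SE − 1.960], with SE = 0.03536 at 80/85 and √(0.32/230) = 0.03730 at 80/80:

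| Margin (assumed) | Control 80%, new 85% | Both 80% |
|---|---|---|
| 5 points | Φ(0.10/0.03536 − 1.960) = 81% | Φ(0.05/0.03730 − 1.960) = 27% |
| 10 points | Φ(0.15/0.03536 − 1.960) = 99% | Φ(0.10/0.03730 − 1.960) = 76% |

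With both rates at 80%, 80% power needs 7.849·0.32/0.05² ≈ 1005 per arm (3015 in total) at 5 points, and 7.849·0.32/0.10² ≈ 252 per arm (756) at 10 points.

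**The case against.** Three stronger readings are tempting, and the document supports none of them.

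- *That the plan can never show non-inferiority.* It can: a significant result favouring a new regimen establishes non-inferiority at any margin. The gap concerns every other result.
- *That P > 0.05 will be reported as success.* The article states no such rule. The 75% and 30% figures would be error rates only if someone adopted it; they show why nobody should. Nor is P > 0.05 always the likely result for a worse regimen: at 10 points worse, a significant difference is the more likely one (70%).
- *That 690 is simply wrong.* It is far too small for the planned test of a 5-point difference, but close to a non-inferiority calculation that takes 5 points both as margin and as assumed advantage.

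The best defence is that one word in the design section carries the non-inferiority claim, while the stated hypothesis is improvement, for which a chi-square test is valid though underpowered. This stands in part: the document does not settle which objective is primary, so the repair cannot presume non-inferiority. Yet the aim of using less PEG makes non-inferiority plausible too, and the label is the declared design. A margin could also sit in a fuller document. That would supply the missing number, but it would not turn the stated two-tailed test of equality into a test against a margin.

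**Conclusion.** The concern holds, and it affects the primary conclusion. The declared design and the fixed primary test do not match, and the wording of the aims adds a second, different objective. As written, the analysis decides non-inferiority only through a significant advantage for a new regimen, about 29% probable per comparison at the article's own 80% and 85%. Otherwise there is no valid decision. The chi-square figures rest on 230 evaluable participants per arm and an 80% control rate. The non-inferiority power and sample-size figures rest also on assumed margins and a one-sided 0.025 level, with 80% power where sample sizes are derived. The mismatch itself depends on none of these.

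**What to change.** State which objective is primary, and make the design label, hypothesis, test and sample size agree.

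**If non-inferiority is primary:**
- Fix and justify a margin before the first unblinding.
- Compare group B with A and group C with A by the two-sided 95% CI for the difference in satisfactory-preparation rate (Newcombe or Miettinen–Nurminen, for instance). Declare non-inferiority when the lower limit lies above minus the margin in both ITT and PP.
- State whether one or both comparisons must succeed; if either suffices, say how the two tests are controlled.
- Use the chi-square test only for superiority, after non-inferiority has been shown.
- Restate power for the chosen margin, both under the assumed 5-point advantage and under equal rates.

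**If superiority is primary:** remove the non-inferiority label from Trial design and setting, and state that 230 per arm gives about 29% power for 80% against 85%.

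**Cost:** a protocol amendment, for which the Protocol amendments section already provides the route, and a less favourable power statement. The analysis uses the same data. The real price is candour about size: with a 5-point margin and equal true rates, 690 participants give 27% power.

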## Discussion

Colonoscopy can be used to visually diagnose intestinal diseases and reduce the incidence of colorectal cancer. The survey showed that the incidence of colorectal cancer in China increases with age [40]. Poor bowel preparation is an important factor that affects the failure of cecal intubation during colonoscopy and leads to a missed diagnosis of some polyps or lesions, which may warrant repeated colonoscopy [41]. There are many studies on modified bowel preparations; however, because of the existence of many adverse reactions or poor medical compliance and tolerance by patients, it is necessary to find safer and more effective bowel preparation methods [42–44]. Currently, many studies have demonstrated the laxative effect of hemp seed oil. However, there is no research on its use in bowel preparation, making it necessary to explore whether 30 mL of hemp seed oil can improve the bowel cleansing potential of PEG in bowel preparation.

We designed a randomized, double-blind, single-center clinical trial to investigate whether 30 mL of hemp seed oil can improve the potential of 2 L PEG for bowel preparation and whether a combination of 30 mL hemp seed oil and 5% sugar brine can reduce the required volume of PEG, as well as reduce the adverse reactions during bowel preparation.

The results of this trial will influence evidence-based decision-making for bowel preparation regimen prescriptions as it will be fundamental in providing reliable recommendations for bowel preparation regimens before colonoscopy.

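### An unadjusted two-tailed P < 0.05 covers every secondary outcome in three arms, with none ordered or labelled exploratory, although reduced adverse effects and better tolerance are a study objective

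*Protocol article*

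**What the plan says.** The Statistical analysis section names the tests for this family: "secondary outcomes will be compared using the chi-square test for categorical variables", with Student's t-test for continuous ones. It then fixes the threshold for all analyses: "All statistical analyses will be conducted with the 2-tailed test, and *P* < 0.05 will be considered statistically significant". No adjustment, testing order or exploratory label is attached to any secondary outcome.

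The Secondary outcomes section first names adverse reactions during preparation as the secondary indicator. It then lists what is evaluated: "We evaluated the interval between taking bowel preparation and the first bowel movement, the total number of bowel movements completed, time of cecal intubation", polyp detection, adenoma detection, willingness to repeat, a 0-to-3 tolerance score, and adverse events. That makes eight if polyps and adenomas are counted separately. The Abstract lists the interval to first bowel movement apart from the secondary indicators, so seven is also a fair count.

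Two of these outcomes are tied to a stated aim. The Objectives section says the trial evaluates the effect of halving PEG with the added agents "on reducing the adverse effects of bowel preparation and increasing the patients’ tolerance of PEG". The Introduction hypothesises that hemp seed oil could "decrease the dosage of PEG without any obvious adverse effects, and increase its acceptance". The Discussion says of the results that "it will be fundamental in providing reliable recommendations for bowel preparation regimens before colonoscopy".

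**The concern.** The article does more than leave multiplicity unmentioned. It states a rule, and taken literally that rule lets any secondary comparison with P < 0.05 be reported as statistically significant, whatever the primary result. A reader would then have no planned basis for separating a result on a stated objective from a chance finding elsewhere in the list.

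This matters because the new regimens are studied for non-inferiority at a lower PEG volume. Better tolerability is much of the reason to adopt such a regimen, so an isolated significant secondary result could easily be taken as support for a recommendation. Settling the primary contrast would not help, because the secondary family would still be open.

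**Working it through.** **Inputs from the protocol article.** Three arms, allocated 1:1:1. Per-test level 0.05, two-tailed. Eight secondary outcomes (or seven). The article states no family-wise error rate, so there is no figure of its own to reproduce. The sample size of 690 does not enter, because the false-positive rate under the null does not depend on it.

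**Not stated, so varied.** (a) How the arms are compared: one test per outcome (a three-group test, or a single contrast), two contrasts with 3 L PEG, or all three pairs. The two-sample tests for continuous variables imply pairwise comparison there; for the chi-square tests the article does not say. (b) The correlation between outcomes, taken as 0, 0.5 or 0.8.

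**Independent-test formula.** With k independent tests, the chance of at least one false positive is 1 − 0.95^k.
- One test per outcome: k = 8, 1 − 0.95^8 = 0.337
- Two contrasts: k = 16, 1 − 0.95^16 = 0.560
- Three pairs: k = 24, 1 − 0.95^24 = 0.708, with 24 × 0.05 = 1.2 false positives expected

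Contrasts that share an arm are not independent, so the last two figures are slightly too high.

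**Simulation allowing for shared arms and correlation.** Each outcome has three independent standard-normal arm means, with a common correlation across outcomes and all nulls true. For each pair, z = difference/√2, rejected if |z| > 1.96. The three-group test is a chi-square on 2 degrees of freedom.

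| Eight outcomes, either direction | corr. 0 | 0.5 | 0.8 |
|---|---|---|---|
| One three-group test each | 34% | 26% | 16% |
| Two contrasts with 3 L PEG | 53% | 41% | 27% |
| All three pairs | 65% | 51% | 34% |

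With seven outcomes at correlation 0 the column is 30%, 48% and 60%.

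**Favourable direction only.** Counting only results in which a new regimen beats 3 L PEG (two contrasts, z > 1.96), the eight-outcome figures are 31%, 21% and 14%. This assumes a favourable direction can be named for every outcome.

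**The two outcomes that carry the objective** (any adverse reaction, tolerance), either direction:

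| Two outcomes | corr. 0 | 0.5 | 0.8 |
|---|---|---|---|
| One three-group test each | 10% | 9% | 8% |
| Two contrasts with 3 L PEG | 17% | 16% | 14% |
| All three pairs | 23% | 21% | 18% |

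The article analyses all data by both intent-to-treat and per-protocol. That adds further, highly correlated tests, which are not counted here.

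**The case against.** The strongest objection is that this is a journal article. Multiplicity for secondary outcomes is commonly left to the full protocol or analysis plan, neither of which is shown, and a general threshold sentence does not declare secondary results confirmatory. That stands in part: the absence of an adjustment scheme is not in itself an error, and no sentence says that one significant secondary result proves a claim. What remains is the rule the article does state. It covers all analyses, with an objective placed on secondary outcomes, and a later plan that ordered or adjusted them would have to override it.

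Three stronger readings are tempting, and the document does not support them.
- A reader might infer that the adverse-effect and tolerance objective rests on all eight outcomes, so that a false claim on it is about as likely as not. Cecal intubation time, detection rates, bowel-movement count and time to first movement do not measure that objective. Figures near 50% belong to the whole list.
- A reader might take 51% (all pairs, correlation 0.5) as the chance of a spurious benefit. It counts both directions and assumes pairwise testing of every outcome. The favourable-direction figure against 3 L PEG at that correlation is 21%.
- A reader might add the reaction types recorded under Safety assessments ("including nausea, vomiting, bloating, abdominal pain, dizziness, vertigo, sweating, dry mouth, and electrolyte imbalance") as nine further tests. That section is an instruction on what to record, and nothing says each type will be tested.

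Some of the supporting text is also softer than it looks. The Introduction's wording on adverse effects is a claim of no obvious harm, and the Discussion's remark on recommendations concerns the trial as a whole.

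**Conclusion.** The point holds in limited form. The article applies an unadjusted two-tailed 0.05 to seven or eight secondary outcomes in three arms and leaves them unordered and unlabelled, while making two of them a study objective. If every null is true, the chance of at least one false-positive secondary result is about 16% to 65% in either direction, and about 14% to 31% in favour of a new regimen over 3 L PEG. For the two outcomes behind the objective, the either-direction chance is about 8% to 10% with one test each, 14% to 17% with two contrasts and 18% to 23% with three.

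These ranges rest on assumed correlations of 0 to 0.8, on all nulls being true, and on a way of comparing the arms that the article does not fully state. The primary outcome is not affected. This is a cheap improvement that limits what may be claimed; it is not a flaw that invalidates the trial.

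**What to change.** In the Statistical analysis section:
- Name the proportion with any adverse reaction during preparation, and the tolerance score, as the only confirmatory secondary outcomes.
- Compare each new regimen with 3 L PEG on both: 2 outcomes × 2 regimens = 4 tests.
- Control the error over those four. One option is Holm (ordered P values against 0.05/4 = 0.0125, then 0.0167, 0.025 and 0.05). Another is a fixed order, adverse reactions then tolerance, within each regimen at 0.05/2 = 0.025.
- State that all other secondary outcomes, any individual reaction types, and the comparison of the two hemp seed oil groups are exploratory. Report them with estimates and unadjusted 95% confidence intervals, without claims of statistical significance.

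Making these tests conditional on the primary result is optional. Statisticians differ on it, and it would first require the primary criterion to be defined, since the article gives neither a margin nor a primary contrast.

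The cost is wording only, with no extra patients or data. The article describes an amendment route and says no testing takes place before the final analysis, so the change can be made before unblinding. The downside is that an isolated P < 0.05 on another secondary outcome can no longer be claimed as a proven benefit, and the four confirmatory tests lose a little power.
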